**Figure 2 f2:**
[figure not shown]
Recruitment and Study Procedure *Note.* The exact time point of each measurement is given in Table 1.

### Therapists

The therapeutic procedures will be conducted by 5 licensed therapists who are working at the outpatient treatment center of the University of Freiburg. All therapist involved in this study had completed a 3-year fulltime psychotherapist CBT training course required and strictly regulated in Germany to obtain a license as clinical psychological psychotherapist. Therapist have between 5 and 29 years therapy experience. Before start of the study, the therapists received 8 hour training consisting of advanced training in CBT skills by [name] (Ohio State University), advanced mental imagery training conducted by [name] (University of Freiburg) and elaborate training on the different protocols for each therapeutic procedure in the study. All therapists will be involved in the delivery of all different procedures.

### Introduction Session

The introduction session will focus on introducing the principles of CBT (central focus will be on the relation between thoughts, behaviors and mood) and completing the CBI. During the CBI, the therapist and patient try to gain insight in the current three most relevant dysfunctional beliefs and current three most relevant dysfunctional behaviors for the patient. These beliefs and behaviors will be used in the subsequent sessions to discuss in relation with depressive symptoms (active control procedure) or to practice CBT skills (CBTSAP and CBTSAP + mental imagery condition). ﻿

### Therapeutic Procedures

All therapeutic procedures use techniques from the protocol for cognitive behavioral therapy (CBT; Beck et al., 1979) for depression and use agenda setting to structure the sessions. In addition, each procedure will focus on targeting the idiosyncratic beliefs and behaviors that were established during the CBI. However, the procedures differ in the number of active ingredients (see Figure 3 and data supplement 1). During the active control procedure, the therapist and patient will focus on discussion of dysfunctional thoughts and behaviors only. Therapists in this condition will be explicitly instructed to focus purely on exploring the relation between dysfunctional thinking and behavior and depressive symptoms, and not to engage in evaluating dysfunctional thinking or behavioral activation. During the CBT skill acquisition procedure (CBTSAP), the therapist and patient will choose one of the cognitive or behavioral skills from a predefined list of CBT skills (i.e., consisting of behavioral activation (behavioral therapy skill) and questions used for evaluating dysfunctional thoughts (cognitive therapy skill). Subsequently, the therapist and patient will discuss how this skill could be or have been applied in past or future situations in which idiosyncratic beliefs and behaviors may (have) lead to negative mood. During the CBTSAP plus mental imagery, the therapist and patient will not only discuss application of the skill but in addition, engage in a mental imagery exercise of skill application. The mental imagery exercise is based on a guided mental imagery procedure and has been shown to increase motivation for goal directed behaviors (Heise et al., 2022; Renner et al., 2019). During the mental imagery procedure, participants are instructed to imagine as vividly as possible and focusing on the positive aspects of the image. The procedure consists of the following steps: 1) imagine the contextual cues (e.g., place, date) of a future or past situation with depressive symptom(s), 2) engaging in multi-sensory imagery of applying the CBT skill in this situation, 3) imaging and experiencing the positive aspects related to successfully applying the CBT skill. All sessions will be videotaped for treatment fidelity checks. Research intervision will take place regularly. The agenda for each therapeutic procedure and the list of CBT skills that can be chosen from and practiced in the CBTSAP procedures is given in data supplement 1 and 2.

**Figure 3 f3:**
[figure not shown]
Therapeutic Elements per Procedure *Note.* Detailed information on the session content can be found in data supplement 1 and 2.

### Instruments

An overview of all patient measurements is given in Table 1. An overview of all measurements completed by the therapists or third observers can be found in Table 2.

**Table 1 t1:** Overview of Patient Instruments per Time Point

Measurement instruments	Baseline	Introduction session	Session 1	Session 2	Session 3	One day after Session 3	Follow-up
Primary outcomes: therapy processes							
*CBT skills*							
Ways of Responding (WOR)	X						X
Behavioral Activation for Depression Scale – short form (BADS-SF)	X	X	X	X	X		X
Cognitive Change Sustained Change (CCSC)	X	X	X	X	X		X
*Idiosyncratic thoughts and behaviors*							
Core Belief Interview (CBI)		X	X	X	X	X	X
*Dysfunctional thinking*							
Cognition Checklist (CCL)	X					X	X
*Reward processing*							
Reward Probability Index (RPI)	X					X	X
Temporal Experience of Pleasure (TEPS)	X					X	X
Secondary outcomes: symptoms							
*Depression*							
Beck Depression Inventory II (BDI-II)	X	X	X	X	X		X
*Symptoms other than depression*							
Brief Symptom Inventory (BSI)	X						X
Potential moderators: Learning capacity							
*Memory functioning*							
Verbal working memory: n-back task	X						
Visual working memory: Single probe detection task	X						
Long-term memory Paired-associates task	X						
*Emotional bias*							
Free viewing eye-tracking task	X	X				X	
Other measures							
*Recall*							
Patient Recall Test (PRT)			X	X	X	X	X
*Diagnostics*							
SCID-5-CV	X						
** *Demographics* **	X						
** *Treatment evaluation* **							X
** *Manipulation check* **			X	X	X		
** *Procedure check* **							X
** *Expected success* **	X		X				

*Note.* CBTSAP = CBT Skill Acquisition Procedure; MI = Mental Imagery; Structural Clinical Interview for DSM-V Clinical Version (SCID-5-CV).

**Table 2 t2:** Overview of Therapist/Observer Instruments per Time Point

Measurement instruments	Baseline	Introduction session	Session 1	Session 2	Session 3	Post-procedure	Follow-up
Therapy processes							
Therapist-rated recall			X	X	X		
Manipulation check							
Therapy integrity							X
Protocol deviations			X	X	X		

#### Primary Outcome: Therapy Processes

##### CBT Skills

CBT skill acquisition will be measured in two different ways. First, before and one week after the therapeutic procedure patients will complete the Ways of Responding (WOR; Barber & DeRubeis, 1992). During the WOR, CBT skills of the participants are tested by asking them to think about themselves in various situations and to tell what they would think and do in such situations. The WOR will reflect the level of CBT skills demonstrated by the patient. Patients will receive three scenarios before treatment and three different scenarios after treatment. Answers to each scenario will be coded into 25 different categories (more categories per answer possible) and given a rating of the overall quality of the response (i.e., the raters’ judgment on how well the response would be in improving mood or adjusting to the individual’s needs, range = 1 (very negatively) to 7 (very positively)). The total score will be composed of the number of responses on positive categories (responses considered consistent with CBT) minus the number of responses on negative categories (depressotypic statements). Interrater reliability showed to be high (ranging from α = .91 to α = .98) and discriminant and convergent validity have been supported (for example: the WOR showed no correlation with a measure of self-control, but was correlated to self-report measure of CBT skills) (Barber & DeRubeis, 2001; Strunk et al., 2014). Second, change in CBT skills during the procedures will be measured using the Behavioral Activation for Depression Scale – short form (BADS-SF) (BA skills) and Cognitive Change Sustained Change (CCSC) (CT skills). The BADS-SF consists of nine items, each rated on a 7-point Likert Scale and internal consistency (α = .81) and construct and predictive validity were supported (for example: the BADS-SF was positively related to measures of reward, negatively related to measures of avoidance and predicted time spent in high and low rewarding behavior; Manos et al., 2011). An example item from the BADS-SF is: ‘There were certain things I needed to do that I didn’t do’. The CCSC consists of 9 items rated on a 7-point Likert scale and internal consistency was supported (α = .93) and the scale showed convergent and discriminant validity by showing a relation with a self-report scale of CBT skills and no relation with a measure of attributional styles (Schmidt et al., 2019). An example item from the CCSC is: ‘I noticed myself thinking less negatively.’

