## Method

### Design

Between-subject experimental design with three parallel conditions, each having an equal length of 3 x 45-minute sessions: 1) Active control procedure (*n* = 50), 2) CBT skill acquisition procedure (CBTSAP) (*n* = 50), 3) CBTSAP with mental imagery (*n* = 50). The Ethic Committee of Freiburg University approved the study (registration number: 20-1022) and the trial is pre-registered at the German Clinical Trial Register (DKTR; registration number: DRKS00024116).

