### Sample Size

Based on a medium effect size, alpha = .05, power =.80, number of experimental conditions = 3, number of repeated measurements = 2 to 4 (G*power (Faul et al., 2007)), a total sample size of 102 to 120 participants would be needed to detect a main effect, and 42 to 57 participants to detect an interaction in a repeated measures ANOVA. Simulation studies suggest 80 to 100 participants to detect an interaction effect between three groups (Shieh, 2019) while simulation studies on multilevel analyses suggest *n* = 80 participants to detect a medium effect size with power =.80 (Aarts et al., 2014). Taking into account 20% drop-out, we aim to include a total of 150 participants.

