### Randomization and Procedure

Patient who are eligible to participate in the study will complete a baseline measurement and an introduction session on different days. The baseline measurement will take place in the lab and includes a measurement of learning capacity. Informed consent will be signed before the baseline measurement. The order of the measurements during the baseline measurement will be randomized for each participant in order to control for potential fatigue effects. The introduction session is conducted by the therapist and focuses on introducing the principles of CBT and completing the Core Belief Interview (CBI; McBride et al., 2007). After the introduction session, patients will be randomized into one of the three conditions ﻿using a computer script performing block randomization (1:1:1, block size = 15). Block randomization will be done by a researcher who is not involved in the study measurements. Randomization will be pre-stratified on severity of depression (mild [Beck Depression Inventory-II (BDI-II) = 14-19] vs. moderate to severe [BDI-II ≥ 20]). Therapy sessions will be completed weekly and the total study procedure from baseline measurement to the post measurement will take a maximum of 5 weeks. The researchers who perform the study measurements are blind for the therapeutic procedures. The full study procedure is also presented in Figure 2. Participants do not receive financial incentives for participation in this study.

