### Data Analyses

All statistical tests will be two-tailed (significance level alpha .05). Descriptives (means, standard deviations) for all measures will be provided for each condition. All analyses will be intention-to-treat and missing data will not be imputed.

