#### Main Analyses

The main analyses will be conducted in Stata. First, to test the direct effects of the different procedures on change in therapy processes and symptoms, differences on the primary and secondary outcomes between conditions (CBTSAP versus active control; CBTSAP versus CBTSAP + mental imagery; active control versus CBTSAP + mental imagery) will be tested using multilevel analysis with maximum likelihood estimation (measurements [Level 1] nested within patients [Level 2] nested within therapists [Level 3]). Because the WOR is only measured at two time points, differences between conditions on the WOR will be tested using a repeated measures ANOVA.

Second, to test whether the effect of the procedures is moderated by individual differences in learning capacity, learning capacity will be added as a moderator in the model. Moderation will be tested by adding learning capacity as a main factor and the interaction between learning capacity and condition to the multilevel regression model. For the WOR, the interaction will be added to the repeated measures ANOVA. Moderation of learning capacity will be tested separately for memory functioning and emotional bias. Memory functioning will be tested separately for each component of memory functioning (i.e., verbal working memory, visual working memory, long-term memory), while controlling for type I error (*p* < .016).

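### Post and follow-up assessments are timed only from Session 3 or the end of the procedure, so none is defined for early stoppers; the WOR ANOVA then becomes complete-case despite the intention-to-treat statement

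*Protocol article*

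**What the plan says.** - **Length of the procedure** (Design): three parallel conditions, "each having an equal length of 3 x 45-minute sessions".
- **Timing of the WOR** (CBT Skills): "before and one week after the therapeutic procedure patients will complete the Ways of Responding".
- **Timing of the other instruments** (Instruments, Table 1): after randomisation the columns are Sessions 1, 2 and 3, "One day after Session 3", and Follow-up. CCL, RPI and TEPS are marked at baseline and in the last two columns only. WOR and BSI are marked at baseline and follow-up only. BADS-SF, CCSC, CBI and BDI-II are also marked at every session.
- **Calendar** (Randomization and Procedure): sessions are weekly, and "the total study procedure from baseline measurement to the post measurement will take a maximum of 5 weeks". Randomisation follows the introduction session.
- **Drop-out** (Sample Size): "Taking into account 20% drop-out, we aim to include a total of 150 participants".
- **Analysis set** (Data Analyses): "All analyses will be intention-to-treat and missing data will not be imputed".
- **Models** (Main Analyses): "Because the WOR is only measured at two time points, differences between conditions on the WOR will be tested using a repeated measures ANOVA". The other outcomes use "multilevel analysis with maximum likelihood estimation".

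**The concern.** A time point counted from Session 3 has no meaning for a patient who never reaches Session 3. The obvious alternative is to read the end of the procedure as the last session attended. That would place an early stopper's assessment weeks before that of a completer, so the two would not be comparable.

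If the schedule is followed as written, the WOR comparison is made among patients who finished all three sessions, while the article describes every analysis as intention-to-treat. The WOR is the first-listed primary measure and the only rater-coded skill test among the primary outcomes. Patients who stop may differ from those who finish. The conditions also differ in content: therapists in the control condition are told not to evaluate dysfunctional thinking or engage in behavioural activation. Equal stopping across conditions therefore cannot be taken for granted, and no later analysis can recover outcomes that were never collected.

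**Working it through.** **1. The plan's own figure.** Inputs from Sample Size: three conditions, alpha 0.05, power 0.80, two to four measurements, medium effect. Assumed, because the article does not give them: f = 0.25 and a correlation of 0.5 between measurements. For the between-condition main effect the noncentrality is λ = f² × N × m / (1 + (m − 1) × ρ).
- m = 2, N = 120: λ = 0.0625 × 120 × 2 / 1.5 = 10.0, power 0.805.
- m = 4, N = 102: λ = 0.0625 × 102 × 4 / 2.5 = 10.2, power 0.811.

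These match the stated range of 102 to 120. Then 120 / (1 − 0.20) = 150, the stated total. The calculation thus budgets for drop-outs who supply no outcome.

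**2. Which primary instruments depend on Session 3 (Table 1).**

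| Instrument | Earliest post-randomisation mark |
|---|---|
| WOR | Follow-up |
| CCL, RPI, TEPS | One day after Session 3 |
| BADS-SF, CCSC, CBI | Session 1 |

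Four of the seven have only a baseline value before the Session 3 anchor. Among the secondary outcomes the BSI is in the same position; the BDI-II is not.

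**3. How many patients.** 0.20 × 150 = 30, or 10 per condition if spread equally. That leaves 120, or 40 per condition.

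**4. What each model does with a baseline-only patient.**
- WOR, two-time-point repeated measures ANOVA without imputation: the patient has no change score and adds nothing to the comparison of change between conditions. The result is a complete-case analysis.
- CCL, RPI and TEPS, multilevel maximum likelihood: the patient stays in with the baseline value. This is valid if the data are missing at random, but the patient adds little information on the treatment effect. With no post-randomisation value on the instrument, little in that model supports the assumption.

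**5. Precision.** √(150/120) = 1.118, so standard errors are about 12% wider than with all 150 assessed. Main-effect power (m = 2, same assumptions) is 0.805 at 120 and 0.890 at 150. The planned N already pays for this loss.

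**6. Bias.** Let a share p of a condition stop, and let stoppers be g SD worse than completers. The completers-only mean is then too favourable by p × g. With the same g in both conditions, the bias in a contrast is g × (p₁ − p₂). All inputs below are assumed.

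| Stopping | g = 0.25 SD | g = 0.5 SD |
|---|---|---|
| 30% vs 10% | 0.25 × 0.20 = 0.05 SD | 0.5 × 0.20 = 0.10 SD |
| 25% vs 15% | 0.25 × 0.10 = 0.025 SD | 0.5 × 0.10 = 0.05 SD |
| 20% vs 20% | 0 | 0 |

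The bias favours the condition that loses more patients. These figures apply directly to the WOR. For CCL, RPI and TEPS only the part of the gap not explained by baseline would bias the contrast.

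**7. Whether a date can be set.** With weekly sessions, Session 3 falls 14 days after Session 1. The post assessment then falls on day 15 and the one-week follow-up on day 21, counted from Session 1. A patient who stops after Session 1 can be given those dates. Timing from the last session attended would instead put that patient's follow-up on day 7, two weeks before that of a completer.

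**The case against.** The strongest reply is that the article is silent, and silence is not exclusion. Nothing in it says that patients who stop are not assessed. A condensed article may leave their follow-up to the full protocol, and the procedure figure is not shown. A reader might infer that early stoppers are deliberately dropped, but the documents do not support that. What stands against the reply is that the article itself fixes the Session 3 anchor, the absence of imputation, the two-time-point ANOVA and the unqualified intention-to-treat statement. Those four do not fit together for anyone without a second WOR.

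Other stronger readings also fail:
- **That intention-to-treat fails for all four instruments.** For CCL, RPI and TEPS the likelihood-based model keeps every patient with a baseline value and is valid under missing at random. The direct conflict is with the WOR.
- **That monitoring of worsening is lost.** The article describes no such check. The BDI-II is taken at every session, so an early stopper keeps values up to the last session attended.
- **That the trial loses power it needs.** The inflation from 120 to 150 covers the 20%.
- **That the control condition will lose more patients.** The conditions share session number and length, therapists and introduction session. Differential stopping is possible, not shown.

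Two further points are fair. Drop-out is not defined in the article, and if it means withdrawal or loss of contact, few of the 30 could be recovered. A fixed interval after the procedure is also a defensible choice for studying direct effects, which argues against re-timing all 150 patients.

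**Conclusion.** The point holds in a limited form. The article defines no post or follow-up time point for patients who stop early. For WOR, CCL, RPI, TEPS and BSI these patients would have baseline data only, and the WOR ANOVA would be complete-case while described as intention-to-treat. Up to about 30 of 150 patients are affected if all planned drop-out is early stopping without later assessment.

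The consequence is possible bias, not lost power. Its illustrated size, 0.05 to 0.10 SD, rests entirely on assumed stopping rates and an assumed gap; it is zero when both are equal across conditions. At the upper end it is one fifth of an assumed standardised difference of 0.5 (0.10 / 0.5). That is modest, but it cannot be repaired once the assessments are missed.

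**What to change.** Keep the Session 3 anchor for patients who complete the sessions. Add a statement that every randomised patient who stops early is invited to the post and one-week assessments, on the dates these would have fallen under the weekly schedule, and that at least the WOR, CCL, RPI, TEPS and BDI-II are collected. For a patient who never starts, count from the date booked for Session 1. The 5-week limit runs from baseline and randomisation comes later, so the text should name the date from which the schedule is counted.

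If these assessments will not be sought, describe the WOR ANOVA as a complete-case analysis instead of intention-to-treat.

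The cost is a few sentences of wording and invitations to about 30 patients for assessments already planned for all 150. Some will decline, and their interval since the last session attended will differ from that of completers.

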
##### Idiosyncratic Thoughts and Behaviors

Idiosyncratic thoughts and behaviors will be measured with the Core Belief Interview (CBI; McBride et al., 2007). This interview will be completed by the therapist during the introduction session. Together the therapist and patient will form an idiosyncratic top three of dysfunctional thoughts and top three of dysfunctional behaviors. Note that the behaviors can both exist of the presence of unhelpful behaviors or the absence of rewarding behaviors. Based on the identified beliefs and behaviors, six idiosyncratic visual analogue scales (VAS) (0-100) will be constructed for each patient (i.e., three dysfunctional beliefs, three dysfunctional behaviors). For the dysfunctional beliefs, credibility of the beliefs and strength of related emotions will be rated. Presence, reward and pleasure related to the behaviors will be measured. The CBI has been used successfully before to establish idiosyncratic dysfunctional thoughts (Bruijniks, Los, & Huibers, 2020; Renner et al., 2018). The exact items of the CBI are given in data supplement 3.

##### General Dysfunctional Thinking

General dysfunctional thinking will be measured using the Cognition Checklist (CCL; Taylor et al., 1997). The CCL consists of 26 items rated on a 5-point Likert Scale and can be divided into two subscale measuring dysfunctional thoughts related to depression versus anxiety. ﻿Internal consistency (ranging from α = .91 to α = .93) and validity was supported in an outpatient sample (i.e. the depression subscale showed a higher relation to other depression measures compared to the anxiety subscale, and the same was shown in the reverse direction; Steer et al., 1994). An example item of the CCL is: ‘When I am with a friend I think: I’ll never be as good as other people are.’

